### Measurements

The principal study measurements are the following:

a) Sociodemographic variables: age, sex, educational level, marital status, family unit.

b) Anthropometric variables and physical evaluation: body weight, height, waist circumference, blood pressure, heart rate, physical activity, lipid profile, blood glucose.

c) Vascular risk factors: smoking, hypertension, diabetes mellitus, dyslipidemia, obesity, alcohol intake.

d) Cardiovascular disease: stroke, heart disease, neuropathy, retinopathy.

e) Drug use (antihypertensive, antidiabetic, lipid-lowering and antiplatelet drugs, psychoactive medication).

f) Comorbidity.

g) Functional grade will be evaluated in reference to daily life activities (both basic and instrumental), and data from an informant will be obtained.

h) Neuropsychological assessment: assessment of the premorbid situation, attention-concentration, speech, logical memory, auditory-verbal learning, visioconstruction memory, visual memory, executive function. Following evaluation, the impairment phases will be classified, ranging from normality to the most severe phases of dementia.

### Measurement instruments

#### 1. Anthropometric measurements

a) Height: the mean of two measurements using a wall meter (Seca 222), with the patient barefoot and in the erect standing position, and measuring to the nearest millimeter. Body mass index: weight (kg)/height (m)^2^.

b) Waist circumference: the mean of three measurements, using a flexible measuring tape at waist level (at the midpoint between the last rib and the iliac crest), parallel to the floor, and measuring after inspiration.

c) Weight: the mean of two measurements using a homologated and easily calibrated scale (Seca 770) with the patient barefoot and lightly clothed. The readings will be rounded to 100 grams.

d) Clinical blood pressure (OMROM M-7): three measurements of systolic blood pressure (SBP) and diastolic blood pressure (DBP) will be made, calculating the mean of the last two readings, and using a validated sphygmomanometer (OMRON M7), following the recommendations of the European Society of Hypertension. Pulse pressure (PP) will be estimated with the mean values of the second and third measurements.

e) Physical activity: Physical activity will be estimated by the 7-day Physical Activity Recall (PAR)[44]. The PAR is a general measure of physical activity, which has been recognized as a valid and reliable tool in recent years, and is widely used in epidemiological, clinical and behavioral change studies. It consists of a semi-structured interview (10-15 minutes) in which the participants provide an estimate of the number of hours dedicated to physical or occupational activities requiring at least a moderate effort in the past 7 days. The categories collected are: moderate, vigorous, and very vigorous physical activity. The dose of physical exercise will be estimated in METs/hour/week, and active persons will be taken to be those doing at least 30 minutes of moderate activity, 5 days a week, or at least 20 minutes of vigorous activity, 3 days a week. Persons not reaching this level of physical activity are regarded as sedentary.

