The relationship between cholesterol and mild cognitive impairment is contradictory. There are several cross-sectional PAPPS studies with differing results [33,34]. There are also several longitudinal studies reporting a positive association between total cholesterol and mild cognitive impairment, while three observe no association, and one reports a negative association [35].

In reference to diabetes mellitus, a number of studies have reported an association with the prevalence of dementia, though others have found no such relationship. Biessesls et al. [36], following an analysis of several longitudinal studies, found the incidence of dementia to increase between 50-100% in subjects with diabetes versus individuals without diabetes. Associations have also been described with blood glucose [37] and glycosylated hemoglobin. In this sense, for every 1% rise in HbA1c, an increased risk of cognitive impairment or dementia has been reported (OR 1.40: CI 1.08-1.83)[38].

Metabolic syndrome groups a series of cardiovascular risk factors; as a result, an increased risk of target organ damage could be expected in patients with this syndrome. However, few studies have evaluated the association between metabolic syndrome and the development of dementia or mild cognitive impairment. Some cross-sectional [39] and longitudinal studies [40] have described an association between metabolic syndrome and cognitive impairment. Thus, while a certain relationship appears to exist, the risk of dementia in individuals with metabolic syndrome has not been firmly established, and it is not clear whether such risk is greater than the sum of its components [38].

Comorbidity among people over age 65 is common and conditions the prognosis of other concomitant disease processes, with an acceleration of the possible complications. Different methods are available for assessing comorbidity. Charlson proposed a numerical scale using a list of pathological conditions: the Charlson comorbidity index [41,42]. This index was designed to classify comorbidities for prognostic purposes, and posteriorly has been used as a control of the influence which comorbidity may exert in different situations. The Charlson index has not been used in the analysis of cardiovascular risk factors and cognitive impairment. Likewise, no study has been made of the association of cardiovascular risk as estimated from the risk scales and cognitive impairment in individuals over 65 years of age.

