Less than one-half of all patients with Alzheimer's disease have been diagnosed, and of these subjects, approximately 25% are receiving some kind of treatment [43]. The number of individuals with undiagnosed cognitive impairment is therefore expected to be high, particularly in groups with certain risk factors. One of the factors explaining why many people with cognitive impairment have not been diagnosed is related to the fact that we have no cognitive impairment screening tool in the elderly population sufficiently warranted by the scientific community and the professionals who care for such patients.

Based on a neuropsychological battery especially adapted for the study of elderly people, we will carry out a study of cognitive performance in people over 65 years of age in Salamanca (Spain), with special emphasis on the identification of early symptoms of cognitive impairment, with the purpose of detecting mild cognitive impairment and of studying the relationships between this clinical situation and cardiovascular risk factors.

The following objectives have been established:

1. To study the cognitive performance of people over 65 years of age in Salamanca, with a view to estimating the prevalence of the different manifestations of cognitive impairment and its severity.

2. To analyze the association of cardiovascular risk factors (diabetes, arterial hypertension, dyslipidemia and metabolic syndrome) in patients over age 65 with mild cognitive impairment.

3. To use the Mini - Mental State Examination (MMSE) and the 7 Minute Screen test as screening tools for cognitive impairment in the elderly population under study.

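### The waist reading is tied to a breath in of unspecified depth, so it may carry an offset that averaging three readings does not remove (minor, relevant only if metabolic syndrome uses a waist cut-off)

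*Protocol article*

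**What the plan says.** Item (b) of 1. Anthropometric measurements sets the procedure: "Waist circumference: the mean of three measurements, using a flexible measuring tape at waist level". It places the tape halfway from the lowest rib to the iliac crest and ends: "parallel to the floor, and measuring after inspiration". Site, tape plane, number of readings and respiratory phase are all fixed. Depth of breath is not, and no other section mentions the phase.

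Waist is one of the principal measurements, in the list "body weight, height, waist circumference, blood pressure, heart rate, physical activity, lipid profile, blood glucose" (Measurements, item b). The second objective in the Background concerns "cardiovascular risk factors (diabetes, arterial hypertension, dyslipidemia and metabolic syndrome) in patients over age 65 with mild cognitive impairment". Of metabolic syndrome the Background says only: "Metabolic syndrome groups a series of cardiovascular risk factors". The article gives no diagnostic criteria for the syndrome and no waist threshold. Obesity appears as a separate item: "Vascular risk factors: smoking, hypertension, diabetes mellitus, dyslipidemia, obesity, alcohol intake". The only obesity-related index with a formula is body mass index, from weight and height (1. Anthropometric measurements, item a).

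**The concern.** Girth between the ribs and the iliac crest changes with breathing, because the lower ribs and abdominal wall move. A reading tied to a breath in, with no stated depth, mixes body size with how far that person breathed in on the day. It could be raised by a deep breath or lowered if the person draws the abdomen in.

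The mean of three readings helps with only part of this. It reduces variation between breaths, but an offset present in all three stays in the mean.

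What is at stake is one of the four exposures named in the second objective. If metabolic syndrome is diagnosed with a waist threshold, an upward shift moves some people over that threshold. The association with mild cognitive impairment is then estimated with a slightly contaminated exposed group, and a larger sample does not cure that.

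**Working it through.** **Plan's own figures.** The article states no waist figure, so there is none to reproduce. Its one design calculation (Power analysis) uses a prevalence of 16%, a margin of 4% and a population of 34,020:

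- n0 = 1.96² × 0.16 × 0.84 / 0.04² = 322.7
- with finite population correction, 322.7 / (1 + 321.7/34,020) = 319.7, which matches the stated 320

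Waist does not enter this calculation, so the sample size does not depend on the measurement rule.

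**Why averaging does not remove the offset.** Write reading j of person i as W_i + s_i + e_ij, where W_i is the resting waist, s_i the person's respiratory offset and e_ij the variation between breaths. The mean of three is W_i + s_i + ē_i. The variance of e falls to one third; s_i is unchanged.

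**Share crossing a waist cut-off.** All inputs here are assumptions: normal waist distribution, SD 10 to 12 cm, uniform upward shift of 1, 2 or 3 cm, and a cut-off z SDs from the median. Share moved above the cut-off = Φ(z) − Φ(z − shift/SD).

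| Shift | Lowest for z = 0 to 0.5 (z = 0.5, SD 12) | Highest (z = 0, SD 10) | Cut-off below the median (z = −0.5, SD 12) |
|---|---|---|---|
| 1 cm | 0.6915 − 0.6615 = 3.0% | 0.5000 − 0.4602 = 4.0% | 2.9% |
| 2 cm | 0.6915 − 0.6306 = 6.1% | 0.5000 − 0.4207 = 7.9% | 5.6% |
| 3 cm | 0.6915 − 0.5987 = 9.3% | 0.5000 − 0.3821 = 11.8% | 8.2% |

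The overall range is about 3% to 12%. In 320 people, the first two columns correspond to about 10 to 13, 20 to 25 and 30 to 38 people crossing the waist criterion. These are not counts of changed syndrome status: a person changes status only if the remaining components leave the diagnosis hanging on waist.

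**Check with variable offsets.** A simulation with SD 11 cm, a true share above the cut-off of 40% to 60%, and shifts of 1, 2 and 3 cm with between-person SDs of 0.5, 1 and 1.5 cm moved 3.4–3.7%, 6.7–7.3% and 9.9–10.9% above the cut-off, and at most 0.04% below it. Waist kept as a continuous variable correlated 0.999, 0.996 and 0.991 with the resting value.

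**Effect on the association, waist criterion alone.** Assume half the participants are truly above the cut-off, an outcome frequency of 16% (the article's planning value for mild cognitive impairment plus dementia), and error unrelated to cognition.

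- For a true OR of 2.0, the risks that satisfy 0.5·p1 + 0.5·p0 = 0.16 are p0 ≈ 0.1145 and p1 ≈ 0.2055.
- A fraction f is moved up from the unexposed group. With SD 11 and z = 0, f = 3.6%, 7.2% and 10.7%.
- Observed risk in the apparent exposed group = (0.5·p1 + f·p0)/(0.5 + f). At f = 0.036 this is (0.1028 + 0.0041)/0.536 = 0.199.

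| Shift | True OR 2.0 seen as | True OR 1.5 seen as |
|---|---|---|
| 1 cm | 1.93 | 1.46 |
| 2 cm | 1.86 | 1.43 |
| 3 cm | 1.81 | 1.41 |

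For a syndrome with several components the attenuation would be smaller.

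**The case against.** The strongest reply is that no misclassification has been shown. The article gives no waist threshold, no criteria for metabolic syndrome and no statement that waist is dichotomised, and a condensed article may leave those to the full protocol. That stands, and it is why the consequence is conditional.

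A reader might infer that obesity is also misclassified. The documents do not support this: obesity is never tied to waist, and the article does define body mass index. Nor do the other three exposures of the second objective (diabetes, arterial hypertension, dyslipidemia) have any stated dependence on waist.

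A reader might also infer that the error is related to the outcome, because impaired participants may follow a breathing instruction differently. That is possible, but nothing in the article shows it, and the Procedure section applies the same procedure to everyone.

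The wording could be a translation slip, or could mean once the breath in is over, that is, on breathing out. This does not rescue the line. If assessors can read it both ways, the data may mix two measurements, and the line needs clarifying either way.

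Finally, it may be said that calling expiration the correct phase relies on an outside convention. The point does not need one. A relaxed end-expiratory state is easier to reproduce than a breath in of unspecified depth, and that is reason enough to prefer it. Because the article does state a phase, this is a rule fixed badly and not a detail left out.

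**Conclusion.** The point holds as a minor measurement improvement. The instruction ties waist to an unstandardised breath and may shift it by an amount that three readings do not average out. Harm to the second objective follows only if metabolic syndrome is classified with a waist cut-off.

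The 3% to 12% range and the modest attenuation rest on the assumed SD, shift, cut-off position and error unrelated to cognition. The article supplies neither the size of the shift nor its direction in an individual. It would go too far to say that the rule enlarges every reading, or that 10 to 38 people would receive a wrong syndrome diagnosis: those counts concern one criterion. Waist analysed as a continuous variable is almost unaffected. Obesity defined by BMI, the prevalence of cognitive impairment and the sample size are not touched.

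**What to change.** In item (b) of 1. Anthropometric measurements, replace the respiratory phase with the end of a normal, relaxed expiration. Keep the site, the tape plane and the mean of three readings.

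If measurement has already begun, keep one phase throughout and report which it was. Then repeat the metabolic syndrome analysis with waist shifted by 1, 2 and 3 cm: downwards for an upward offset and, since the individual direction is unknown, upwards as well if wanted.

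The cost is one line in the measurement instructions, with no extra time, staff or equipment. The sensitivity analysis is a recoding of data already collected.

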#### 2. Cardiovascular risk and stroke risk scales

Estimated risk at 10 years will be calculated according to the Framingham risk scales for stroke and global cardiovascular morbidity-mortality [22].

#### 3. Measurement of comorbidity

The disorders established by Charlson in the original article published in 1987 [41] are: myocardial infarction; congestive heart failure; arterial hypertension; peripheral vascular disease; cerebrovascular disease; dementia; chronic pulmonary disease; connective tissue disease; peptic ulcer; mild, moderate or severe liver disease; diabetes with or without organ damage; hemiplegia; leukemia; lymphoma; solid tumor with metastasis; AIDS; and moderate or severe kidney disease. After establishing patient comorbidity, each entity will be scored in a table - the sum of the scores representing the Charlson comorbidity index (CCI). In order to calculate the age-adjusted Charlson comorbidity index (ACCI), we add one point to the CCI for each decade above 50 years of age. The values obtained will be grouped into four categories: 1-2, 3-4, 5-7 or ≥ 8.

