### Statistical analysis

A descriptive analysis of the data will be made, establishing comparisons with the baseline evaluation of the previous study. Posteriorly, an analysis will be made of the qualitative variables using the chi-squared test, and the qualitative and quantitative variables will be analyzed using the Student t-test and analysis of variance (ANOVA), depending on whether two or more categories are involved. An analysis will be made of the correlations of the quantitative variables, together with multiple regression analysis to identify the variables associated with cognitive impairment diagnosed by the neuropsychological tests.

Likewise, an evaluation will be made of the sensitivity, specificity and predictive values of the tests employed in screening for cognitive impairment, using the neuropsychological evaluation made as gold standard.

Lastly, we will analyze the evolution of the different parameters between the two evaluations made, attempting to identify those variables with greater predictive capacity in reference to the evolution of cognitive impairment.

The information will be analyzed according to the place of residency, age and sex of the patient, the family situation and patient cognitive impairment, risk factors and comorbidity index.

Data input will be made using the Teleform system, with a questionnaire previously designed for the project, and exporting the data to the SPSS statistical package for posterior analysis.

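### The comorbidity index scores dementia, hypertension and diabetes (and age, when age-adjusted), so relating it to cognitive impairment is partly circular where the outcome includes dementia

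*Protocol article*

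**What the plan says.** The section on measurement of comorbidity lists the scored disorders. They include "myocardial infarction; congestive heart failure; arterial hypertension; peripheral vascular disease; cerebrovascular disease; dementia; chronic pulmonary disease" and "diabetes with or without organ damage". The item scores are summed with none left out. For the age-adjusted version, "we add one point to the CCI for each decade above 50 years of age", and the result is grouped into four categories starting at 1-2.

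Dementia is also part of the outcome. The power analysis uses a combined prevalence of mild cognitive impairment and dementia of 16%, and both the measurement list and the Global Deterioration Scale run from normal to severe. Participants with dementia are not excluded. Hypertension and diabetes are named exposures in Objective 2.

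The Statistical analysis section plans "multiple regression analysis to identify the variables associated with cognitive impairment diagnosed by the neuropsychological tests". In a separate sentence it says the data will be analysed by residence, age, sex, family situation and "patient cognitive impairment, risk factors and comorbidity index". The Background presents the index as new to this question: "The Charlson index has not been used in the analysis of cardiovascular risk factors and cognitive impairment".

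**The concern.** A score that contains the outcome will tend to be higher in people who have the outcome. A participant whose dementia is recorded gains index points for that reason alone, so part of any link between comorbidity and impairment reflects how the score is built. The Background presents this use of the index as new, so such a link could be reported as a finding.

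Hypertension and diabetes raise a second problem. If the index stands in a model beside them, each is counted once in its own term and again inside the index. The exposure coefficient then no longer measures the whole effect of the exposure. The age-adjusted version does the same with age, which the analysis also uses separately.

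**Working it through.** **The plan's own figure.** With p = 0.16, margin 0.04 and two-sided alpha 0.05, n = 1.96² × 0.16 × 0.84 / 0.04² = 322.7. With the finite population of 34,020 it is 322.7 / (1 + 321.7/34,020) = 319.7. The stated 320 reproduces and is used below.

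**Inputs from the article.** 16% impaired (Power analysis); 8% demented and 65% hypertensive (Background); fewer than half of Alzheimer cases diagnosed (Background), which is why the share of dementia recorded in the index is varied.

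**Assumptions.** One point per condition (the scoring table is not shown); other comorbidity unrelated to impairment unless stated; index SD 1.1 to 2.0.

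**Step 1: built-in difference.** The impaired exceed the unimpaired by r × 0.08/0.16 = 0.5r points, where r is the share of dementia recorded. At the article's regional dementia figure of 6.4%, it is 0.4r.

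**Step 2: false-positive rate.** Group sizes are 320 × 0.16 = 51.2 and 268.8. The standard error is SD × √(1/51.2 + 1/268.8) = 0.1525 × SD, that is 0.168 at SD 1.1 and 0.305 at SD 2.0. With z = difference/SE, the approximate rejection rate is Φ(z − 1.96) + Φ(−z − 1.96).

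| Dementia recorded | Difference | z (SD 1.1 / 2.0) | Approximation | Simulation |
|---|---|---|---|---|
| 25% | 0.125 | 0.75 / 0.41 | 12% / 7% | 12% / 9% |
| 50% | 0.25 | 1.49 / 0.82 | 32% / 13% | 31% / 15% |
| 100% | 0.50 | 2.98 / 1.64 | 85% / 37% | 82% / 38% |

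With no dementia recorded the rate is about 5%.

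**Step 3: exposure in the same model.** Let the index be I = H + D + R + C (hypertension, diabetes, recorded dementia, other comorbidity). In logit P = a + βH + γI, hypertension carries β + γ in total. The fitted β is therefore roughly the true log odds ratio minus γ, so the fitted odds ratio is about the true one divided by the index odds ratio per point. Simulated with hypertension and dementia in the index, a true hypertension odds ratio of 2.0 and null comorbidity, the fitted value is 1.42 to 1.92 across the recording shares and SDs above. The low end comes with full recording and the narrow SD. One such run gave an index odds ratio of 1.42 and a hypertension odds ratio of 1.43; the rule gives 2.0/1.42 = 1.41.

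A second simulation had 400,000 subjects per scenario, diabetes also in the index, and a narrower comorbidity spread (Poisson, mean 0.6, SD √0.6 = 0.77). Its further assumptions were diabetes in 20% and an age odds ratio of 1.08 per year. True odds ratios of 1.5 with half of dementia recorded were fitted at about 1.04 with the CCI and 1.08 with the age-adjusted version. The spurious CCI odds ratio was 1.43 per point. Taking the overlapping items out restored about 1.5.

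**Step 4: mild cognitive impairment against normal, dementia cases left out.** With null comorbidity, the exposure odds ratios stay at their true values (about 2.0 and 1.5 in the two set-ups). If other comorbidity has an odds ratio of 1.2 per point, 1.5 falls to about 1.21-1.26; the rule gives 1.5/1.2 = 1.25.

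**Step 5: age.** By the stated rule, a 90-year-old with no disease has four points and falls in category 3-4. This affects only the age-adjusted version.

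**The case against.** A reader might infer that an association is guaranteed and that the hypertension and diabetes estimates of Objective 2 are necessarily pulled toward the null. The documents do not support that reading.

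- **Objective 2 concerns mild cognitive impairment.** If dementia cases are left out of that contrast, the dementia item does nothing (Step 4). This stands. Dilution there requires a real effect of other comorbidity.
- **The model is not written out.** The regression sentence names no covariates. The index appears in a separate list that also contains cognitive impairment itself, so that list may describe breakdowns of the data. This stands in part: dilution needs the index and the risk factors in one model, which the text implies but does not specify. The circular association needs no such model, because comparing the index by impairment status is enough.
- **Full recording is an upper bound.** The article says fewer than half of Alzheimer cases are diagnosed, and it does not say whether the dementia item is taken from prior diagnosis or from the study battery. The methodological limitations name mental impairment as a cause of loss, which may lower the dementia share below 8%. This stands, and is why a range is given.
- **An article may leave detail to the full plan.** This does not answer the point. The items, the summing, the age points and the categories are all stated, and it is this stated construction that conflicts with the stated use.
- **Comorbidity is in none of the three objectives.** This is true and lowers the severity. Prevalence and screening accuracy are unaffected.

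**Conclusion.** The overlap is explicit in the text. Where the outcome includes dementia, a positive association between index and impairment is built in on average, in proportion to how much dementia the index records. Under the stated assumptions the false-positive rate is about 9-12%, 15-31% or 38-82% at 25%, 50% or 100% recording, against a nominal 5%. A true hypertension odds ratio of 2.0 is fitted at about 1.4-1.9 if the index shares the model. The size depends on assumed item scores, index spread and recording. The downward direction for the exposures holds whenever the index coefficient is positive.

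For mild cognitive impairment against normal without dementia cases, there is no dementia circularity. The exposure estimates are diluted only if other comorbidity truly matters, with 1.5 falling to about 1.2-1.3 at an odds ratio of 1.2 per point. The age overlap is confined to the age-adjusted index and is minor for the exposure estimates.

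This is a should-fix point: comorbidity is not itself an objective, and the index can be re-derived from items already collected.

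**What to change.** State in the Statistical analysis section that analyses of cognitive outcomes use a modified index. It omits dementia, omits hypertension and diabetes whenever these are in the model, and carries no age points. Age enters as its own covariate. Keep the full CCI, the age-adjusted version and its four categories for describing the sample. Omitting cerebrovascular disease as well is optional, since it is not an Objective 2 exposure.

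The cost is one sentence and one derived variable, with no new measurement. The downside is that the modified index cannot be compared directly with published index values, which is the reason to keep the full index in the descriptive tables.
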